## Abstract

**Background:**

Mechanical ventilation (MV) is one of the most utilised techniques in the intensive care unit (ICU), but it can cause sequelae that can negatively influence the patient’s health-related quality of life (HRQL). Nursing-sensitive outcomes (NSOs) can also influence the HRQL. Assessing the HRQL of mechanically ventilated patients admitted to an ICU and its relation to nurse-sensitive outcomes will give healthcare professionals with valuable information to improve patient care.

**Methods:**

Prospective longitudinal cohort study in which all patients admitted to the ICU at *Hospital Universitari Vall d’Hebron* who undergo MV for more than 48 h will be included. The study will last 12 consecutive months. HRQL will be assessed by the completion of the SF-36 and the Saint Georges Respiratory Questionnaire. Pre-admission HRQL assessment will be performed by the main caregiver, and after ICU discharge, the assessment will be performed by the patient him/herself. The same questionnaires will also be completed one year after ICU discharge. Other variables (sociodemographic and those related to reason for ICU admission, ICU length of stay, MV, ICU stressors and NSO) will be included in a multiple regression model to assess their relation to the patient’s HRQL.

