#### Secondary objectives

To determine whether there are any differences in HRQL in mechanically ventilated patients prior to admission into ICU and one year after discharge from the ICU.To identify whether there is any relationship between the duration (in days) of mechanical ventilation and HRQL one year after discharge from the ICU.To identify whether there is any relationship between NSO and HRQL of mechanically ventilated patients one year after discharge from the ICU.To identify differences between the patient’s own assessment of HRQL and the main caregiver’s perception.To identify stressors that mechanically ventilated patients admitted in ICU identify when discharged and which ones last for at least one year after they have left the ICU.To identify whether there is a relationship between the amount and type of stressors perceived by mechanically ventilated patients during their admission and their HRQL one year after discharge from the ICU.

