### Data analysis

A descriptive analysis will be carried out for all variables. Mean and standard deviation will be utilised for quantitative variables that follow a normal distribution. For the rest of the variables, the median, maximum and minimum values will be used. Qualitative variables will be described utilising absolute frequencies and percentage values for each category.

Statistical analysis of HRQL results will be performed on the questionnaire’s different dimensions as well as on the questionnaire as a whole. To compare the results obtained at the time of ICU discharge with those obtained one year after discharge, Student’s t-test or Wilcoxon test will be applied to the paired data depending on the variable distribution. This analysis will also depend on the length of MV.

A multiple regression model will be elaborated utilising HRQL as the result variable. Relevant clinical situations (number of transfusions and surgical interventions, pressure ulcers, nosocomial infections…) will be considered as independent variables. All analysis will be performed with a 95 % confidence interval.

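### The single regression adjusts ventilation days for their own consequences, so it does not answer objective 2 and answers objective 3 only in part

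*Protocol article*

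**What the plan says.** - **Abstract, Methods.** The list of variables runs from sociodemographic data and reason for admission to "ICU length of stay, MV, ICU stressors and NSO) will be included in a multiple regression model".
- **Data analysis.** Again one model is described: "A multiple regression model will be elaborated utilising HRQL as the result variable". Its regressors are an open list of clinical events: transfusions, surgery, "pressure ulcers, nosocomial infections…) will be considered as independent variables".
- **Secondary objectives.** The second asks about the "relationship between the duration (in days) of mechanical ventilation and HRQL one year after discharge from the ICU". The third asks about the "relationship between NSO and HRQL of mechanically ventilated patients one year after discharge from the ICU". The sixth asks the same about stressors.
- **Other use of ventilation length.** For the paired comparison of discharge with one year, Data analysis adds: "This analysis will also depend on the length of MV".
- **Intended reading.** The Abstract's Discussion speaks of the impact of ventilation, nursing-sensitive outcomes and stressors, and expects it to guide early nursing interventions. The main Discussion speaks of their effect.

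**The concern.** A coefficient in a multiple regression is conditional on everything else in the model. If some of the other regressors are consequences of the exposure, the part of its influence that runs through them is removed. Longer ventilation can lower later quality of life by giving more time for pneumonia, pressure ulcers and stressful airway experiences, and by lengthening the stay. With all of these in the model, the coefficient of ventilation days keeps only what does not pass through them.

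A small or null coefficient could then be read as showing that ventilation length, or preventing a nursing-sensitive event, matters little. Nursing-sensitive outcomes are the main objective and the results are meant to steer care, so that misreading would count. Objective 2 has no second route. The paired test concerns change between discharge and one year, and however ventilation length enters it, it does not relate ventilation days to the one-year level.

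**Working it through.** **1. Order of the variables, from the article itself.**

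- *Ventilation before complications.* The Background says most complications of ventilation go with its duration. It does not name them, but Table 1 counts ventilator-associated pneumonia, pressure ulcers and other infections as nursing-sensitive outcomes.
- *Ventilation before stressors.* The Background describes the ICU-SEQ as covering problems that arise from intubation and ventilation. Table 1 measures it at ICU discharge.
- *Length of stay last.* It is known only at discharge and includes the ventilated ICU days.

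For objective 2, the nursing-sensitive outcomes, stay and stressors therefore lie largely downstream of the exposure. For objective 3, stay and stressors plausibly do. For objective 6, ventilation and nursing-sensitive outcomes mostly come before the exposure.

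**2. Illustration of size.** The article gives no figure to reproduce: the Sample size section has only a count (360 eligible, 200 expected) and no effect size. All path sizes below are assumptions.

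Severity affects every variable. Ventilation (MV) acts on nursing-sensitive outcomes (NSO), stay and stressors with link a. NSO acts on stay and stressors with link a. NSO, stay and stressors each act on quality of life with b. The direct effect of MV is d = −0.3.

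- NSO: total = b + 2ab. Single-model coefficient = b. Share = 1/(1 + 2a).
- MV: total = d + a(b + 2ab) + 2ab = d + 3ab + 2a²b. Single-model coefficient = d. Share = d/(d + 3ab + 2a²b).

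| a | b | MV total | MV share | NSO total | NSO share |
|---|---|---|---|---|---|
| 0 | either | −0.300 | 100% | b | 100% |
| 0.1 | −0.1 | −0.332 | 90% | −0.120 | 83% |
| 0.1 | −0.3 | −0.396 | 76% | −0.360 | 83% |
| 0.3 | −0.1 | −0.408 | 74% | −0.160 | 62.5% |
| 0.3 | −0.3 | −0.624 | 48% | −0.480 | 62.5% |
| 0.5 | −0.1 | −0.500 | 60% | −0.200 | 50% |
| 0.5 | −0.3 | −0.900 | 33% | −0.600 | 50% |

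A simulation of 400,000 patients agreed with these shares to within about two percentage points. Adjusting only for what precedes the exposure recovered the totals: at a = 0.3, b = −0.3 it gave −0.625 for MV (true −0.624) and −0.479 for NSO (true −0.480).

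**3. Stressors.** In the same scenario the single model gave −0.300 against a true −0.300. The unadjusted coefficient was −0.713. Adjustment for ventilation, NSO and stay is needed here.

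**4. Unmeasured cause.** With an added unmeasured cause of NSO, stay and quality of life, the NSO total was −0.480. The single model gave −0.418 and the upstream-only model −0.742, so both were wrong. For MV (true −0.624), the single model gave −0.202 and the upstream-only model −0.624.

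**The case against.** **The objectives speak only of a relationship, and a conditional association is one.** This stands in part: the single model's coefficients are valid as conditional associations. But the article reads them as impact and effect, and nowhere says that a direct effect is meant.

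**An article condenses, and covariate sets belong in the full protocol.** That excuses a missing list. It does not excuse a stated choice, and the Abstract does state that these groups enter one model.

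**The article does not clearly enter ICU days beside ventilation days.** This stands. The Abstract's groups resemble the category labels in Table 1, where ICU length of stay is also the heading for diagnosis, APACHE II, surgery and more. Data analysis names neither ICU days nor ventilation days. A reader might infer near-collinearity, wide intervals and flipped signs. That would need a correlation the article does not give.

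**Objective 6 might seem to be hit as well.** It is not. Ventilation and nursing-sensitive outcomes mostly precede the stressors, and the article places no consequence of stressors in the model.

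**For objective 3, removing variables is no clean cure.** This stands. Ventilation time before a pneumonia is a confounder, and ventilation time after it may be a consequence. A set limited to admission factors would leave out the confounder. Under the unmeasured cause in step 4, the single model was even closer to the truth for nursing-sensitive outcomes.

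**Conclusion.** The point holds for objective 2. If the single model is fitted as the Abstract states, the coefficient of ventilation days is at most a residual direct effect, and no other stated analysis relates ventilation days to one-year quality of life. It holds more weakly for objective 3, where adjustment for later stay and stressors may remove part of the effect. It does not hold for objective 6.

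A reader might infer that the estimates will be too small by a known fraction, such as half. The documents do not support that: the shares in the table depend entirely on assumed links, and the loss is nil when the links are zero. Nor is the model invalid in itself. It answers a different question from the one objective 2 asks, and the article does not say so.

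**What to change.** **Objective 2.** Fit a 12-month quality-of-life model with ventilation days as a continuous term. Adjust only for pre-exposure factors: age, sex, Charlson index, APACHE II, reason for admission, and caregiver-reported pre-admission quality of life. Leave out ICU length of stay, nursing-sensitive outcomes and stressors. Confirm that the caregiver form refers to the time before admission: the Abstract says so, while Table 1 and Data collection give only when it is completed.

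**Objective 3.** Leave out ICU length of stay, stressors and other events after the nursing-sensitive outcome. Adjust for baseline factors and for ventilation time before the first such event, instead of total ventilation days. Table 1 records ventilation modes and nursing-sensitive outcomes daily, so this can be built. State a reference day for patients without an event. Say over what window pain hours and nurse expertise are measured, since these have no event date.

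**Objective 6.** Keep adjustment for ventilation and nursing-sensitive outcomes.

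**Single model.** Keep it as secondary, describe its coefficients as conditional associations, and align its regressors between the Abstract and Data analysis.

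**Cost.** A few extra models and tables on data already planned. Residual confounding remains, most of all for objective 3, where ventilation and nursing-sensitive events can influence each other.

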**Discussion:**

This study will show the relationship between the HRQL perceived by patients and their main caregiver, what the HRQL is one year after discharge from ICU, and what the impact of MV, NSO and ICU stressors and other clinical outcomes on the patient’s HRQL is. Determining mechanically ventilated patients’ HRQL and its relation to NSO and ICU stressors as well as other clinical variables will enable early nursing interventions to try to minimise possible sequelae and improve the patient’s welfare.

**Trial registration:**

*ClinicalTrials.gov ID:*NCT02636660*Registration Date:* 17th December 2015.

## Background

Mechanical ventilation (MV) is one the most utilised therapeutic techniques within the intensive care unit (ICU). It is commonly used to support patients diagnosed with severe respiratory failure [1], but several complications have been documented in the literature [2] that can appear during both the acute phase of treatment and in later phases, becoming a chronic problem in some cases. Most of these complications are related to the length of treatment [3–5], and they could affect patients’ health-related quality of life (HRQL).

HRQL conceptualisation is vital for the analysis and evaluation of health-related outcomes. Knowing the patient’s health perception, his wishes and motivating factors when making decisions related to his own health as well as applying procedures to evaluate healthcare providers, is essential to the definition of HRQL.

Diagnosis and treatment of illness exclusively at a biomedical level in addition to technologically advanced procedures represent a qualitative improvement in patient survival in recent decades, but they have reduced a more holistic approach to health care because they only fight against illness without promoting patient welfare. From a more holistic perspective, and in an attempt to quantify the contribution of nursing to health-related outcomes, the term “nursing-sensitive outcome” (NSO) was created. According to the National Quality Forum, those indicators that are sensitive to certain nursing interventions are measurements of the process’ structure (the process itself and its outcomes) and are affected or influenced by the intervention of nurses, although the responsibility is shared with other professionals. The forum agreed on several NSO standards such as pressure ulcer care, infection control, falls prevention, expertise of the nursing team, patient satisfaction and HRQL [6].

Outcome evaluation and knowledge of HRQL in mechanically ventilated critical care patients is vital to understand how this therapeutic technique affects patients and therefore designing care strategies for both acute and later phases of treatment. The goal is to minimize unwanted effects and improve cost-effectiveness, always considering the patient’s perspective during the decision-making process.

The analysis of factors that determine the patient’s perception on HRQL during the different phases of illness as well as the adaptation process of unwanted results will give us in-depth knowledge of the mechanisms that affect their HRQL in a negative way and therefore plan interventions to promote the optimal patient welfare [7].

There is a great deal of published literature on mechanically ventilated patient’s HRQL. All authors agree that the quality of life perceived by these patients is worse than that perceived by the reference population [4, 8–11], although determinants of HRQL are not well defined. Additionally, differences among critical care units (surgical, cardiac, general) and the variety of tools utilised to measure HRQL make it hard to compare results [11].

Highly specialised ICUs constitute a very stressful environment for the patient, which has been related to the onset of delirium or an acute confusional state in different phases of the disease, but other mid and long-term repercussions such as memory loss, delusion and other neurophysiological disturbances that have an effect on HRQL perception have been described [12–14].

Some authors have studied factors that have a stressful effect on mechanically ventilated patients [15–18] and have found that one of the worst remembered and most stressful experiences, aside from thirst and pain, is endotracheal tube discomfort [19]. There are several tools to assess stressors within ICU, and all of them allow us to assess the degree of stress or nuisance experienced by the patient for each factor. One of the most well-known is the Intensive Care Unit Environmental Stressor Scale (ICUESS), which allows us to perform a global evaluation of the ICU but does not take into account problems secondary to tracheal intubation or MV. Another tool recently described in a HRQL study on mechanically ventilated patients is the ICU Stressful Experience Questionnaire (ICU-SEQ), which evaluates the general aspects of an ICU setting but also emphasizes those problems that originated as a result of orotracheal intubation and MV [12, 14, 15].

Knowing what HRQL is, its stressors and which NSO have an influence on it should allow us to design and implement strategies and nursing care plans to minimise negative effects and address chronic problems, thereby improving the patient’s welfare, security and quality of life.

## Methods/design

### Aims

#### Main objective

To assess health-related quality of life of mechanically ventilated patients admitted in an ICU and its relation to nursing-sensitive outcomes.

#### Secondary objectives

To determine whether there are any differences in HRQL in mechanically ventilated patients prior to admission into ICU and one year after discharge from the ICU.To identify whether there is any relationship between the duration (in days) of mechanical ventilation and HRQL one year after discharge from the ICU.To identify whether there is any relationship between NSO and HRQL of mechanically ventilated patients one year after discharge from the ICU.To identify differences between the patient’s own assessment of HRQL and the main caregiver’s perception.To identify stressors that mechanically ventilated patients admitted in ICU identify when discharged and which ones last for at least one year after they have left the ICU.To identify whether there is a relationship between the amount and type of stressors perceived by mechanically ventilated patients during their admission and their HRQL one year after discharge from the ICU.

### Design

This is a prospective longitudinal cohort study.

### Setting

The study will be carried out at the Intensive Care Unit of the *Hospital Universitari Vall d’Hebron*, located in Barcelona, Spain, which is a high-complexity hospital and a referral centre for many disease processes at a national level.

### Subjects of study

All mechanically ventilated patients who fulfil the selection criteria outlined below were enrolled in the study:

#### Inclusion criteria

Over 18 years old.Mechanical ventilation for more than 48 h.Voluntary participation (signed informed consent).

#### Exclusion criteria

Patients admitted from other ICUs that had been mechanically ventilated for more than 48 h at the time of admission to our centre.Patients with domiciliary respiratory support.Mentally or psychologically impaired patients (unable to comprehend the questionnaire).Patients who do not speak Spanish fluently.Patient without a permanent address (unable to do a proper follow-up).

#### Sample size

According to data previously collected in our department, a total of 360 patients should meet the inclusion criteria during the study timeframe. Assuming possible losses and a high mortality rate within critical care, the final cohort is expected to be 200 patients.

#### Sampling technique

A non-probabilistic convenience sampling will be used, including patients as they are admitted to the ICU.

### Variables

The following variables will be collected: anthropometric and sociodemographic data and data related to ICU admission, mechanical ventilation, NSO, HRQL and ICU stressors. Variable definitions and the data collection schedules are summarized in Table 1

**Table 1 Tab1:** Variables and Measurement Schedule

Category	Variables	Measurement Schedule
Anthropometric	Age, Gender	Admission
	Weight, Height	Admission and 12 months after ICU discharge
Sociodemographic	Academic level	Admission and 12 months after ICU discharge
	Employment, economic income	
	Main caregiver, family/social support system	
ICU length of stay	Main medical diagnosis, reason for ICU admission, APACHE II, Age corrected Charlson Index	Admission
	ARDS, MODS, Surgical interventions, blood transfusion, renal replacement therapy, Ramsay Score for >3 hours.	Daily
	Complications, GCS, Barthel Index, length of ICU stay (days) and hospital stay	ICU discharge and 12 months after
		ICU discharge and hospital discharge
Mechanical Ventilation	Reason for intubation and MV	Admission
	Modes of MV utilised (hours and days)	Daily
	Respiratory complications	
	Days with tracheostomy tube in place	ICU Discharge
	Days on MV	
NSO	Total hours in pain (Assessed using a VAS), PU, Falls, VAP, CRB, UTI	Daily
	Allocated nurse’s expertise	
HRQL	SF-36, QRSG	ICU discharge and 12 months after
	SF-36, QRSG (assessed by main caregiver)	ICU discharge
ICU Stressors	ICU-SEQ	ICU discharge and 12 months after

APACHE II: Acute Physiologic A Chronic Health Evaluation II, ARDS: Acute Distress Respiratory Syndrome, MODS: Multiorgan Dysfunction Syndrome, GCS: Glasgow Coma Score, ETT: Endotracheal Tube, MV: Mechanical, VAS. Visual Analog Scale, PU: Pressure Ulcers, VAP: Ventilator Associated Pneumonia, CRB: Catheter Related Bacteriemia, UTI: Urinary Tract Infection, SF-36: Medical Outcome Study-Short Form 36, QRSG: Saint Georges Respiratory Questionnaire, ICU-SEQ: ICU Stressful Experience Questionnaire

.

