### Data collection

Data will be collected over 12 consecutive months. Patient selection for the study cohort will be performed by the research team by evaluating all patients who may need or had needed MV. Follow up documentation will be provided for all mechanically ventilated patients. When a patient has been mechanically ventilated for over 48 h, informed consent will be obtained from the next of kin. From that moment, all patient data from their medical records will be gathered until MV is discontinued.

One week after the patient has been discharged from the ICU, informed consent will be obtained from the patient. Approaching the patient earlier is considered to be inappropriate by the research team. If the patient agrees to participate in the study, the SF-36, SGRQ and ICU-SEQ questionnaires will be provided for the patient to complete. The same questionnaires will be given to the main caregiver at that time. One year after ICU discharge, the same questionnaires will be completed again to assess the persistency of stressors’ sequelae.

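### The pain outcome is a raw total of VAS-rated hours in ventilated patients with no count of assessable hours, so it mixes pain with sedation and days on ventilation

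*Protocol article*

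**What the plan says.** The article's Variables section refers the reader to Table 1 for variable definitions. In the NSO block, the items collected daily are "Total hours in pain (Assessed using a VAS), PU, Falls, VAP, CRB, UTI", and the table's footnote expands the abbreviation as "VAS. Visual Analog Scale". No other pain tool for the ICU stay is named. Table 2 adds only the pain dimension of the SF-36.

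The patients and the time window are set elsewhere:

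- Inclusion criteria: "Mechanical ventilation for more than 48 h".
- Data collection: "From that moment, all patient data from their medical records will be gathered until MV is discontinued". The hours gathered are therefore ventilated hours.
- Data collection, on consent during ventilation: "informed consent will be obtained from the next of kin". The patient is first approached one week after ICU discharge.
- Table 1, in the ICU length of stay block, also daily: "Ramsay Score for >3 hours". Sedation is tracked but not linked to the pain variable.

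The main objective relates HRQL to the NSOs. The abstract's Methods paragraph sends the NSOs, together with the ICU-stay and ventilation variables, into a multiple regression on HRQL.

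**The concern.** The other clinical events in the same row (pressure ulcers, falls and the three infections) can be established without the patient's own report. Pain measured by VAS, on its usual reading, cannot. Ventilated patients may be sedated for part of the collected period, and a sum of hours in pain gains nothing from an hour in which no rating could be made. Without a denominator, a low total can mean well-controlled pain, few ratable hours or a short period on ventilation.

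The share of unratable hours plausibly follows sedation, and sedation plausibly follows severity, which may itself relate to HRQL at one year. If so, the measurement error is not random with respect to the outcome. At stake is the coefficient for one of the seven NSO items in Table 1, and so part of the exposure in the main objective.

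**Working it through.** The article gives no figure to reproduce here. The check is a simple model of how the recorded total behaves.

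**Inputs.** The metric (total hours), the instrument (VAS), the daily schedule and the window ending with ventilation come from Table 1 and the Data collection section. The article does not give the next three quantities, so their values are assumptions:

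- D = days observed on ventilation
- p = share of hours in pain, set at 0.30 for everyone
- u = share of hours in which a VAS cannot be obtained

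**Formulas.**

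- Hours in pain = 24 × D × p
- Assessable hours = 24 × D × (1 − u)
- Recorded total = 24 × D × p × (1 − u), since unrated hours add nothing

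**Results.**

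| Patient | D | u | Hours in pain | Assessable hours | Recorded total | Recorded ÷ assessable |
|---|---|---|---|---|---|---|
| A | 5 | 0.2 | 36.0 | 96.0 | 28.8 | 30% |
| B | 5 | 0.8 | 36.0 | 24.0 | 7.2 | 30% |
| C | 14 | 0.7 | 100.8 | 100.8 | 30.2 | 30% |
| E | 14 | 0.9 | 100.8 | 33.6 | 10.1 | 30% |

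**Reading the table.**

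1. A against B: same days and same pain, but the totals differ by 28.8 ÷ 7.2 = 4-fold. The whole difference is assessability.
2. A against C: C has 100.8 ÷ 36 = 2.8 times the hours in pain, but the recorded totals are nearly equal (30.2 ÷ 28.8 = 1.05).
3. A against E: the order reverses, with E recording 10.1 ÷ 28.8 = 0.35 of A's total.
4. In every row the fraction of pain hours lost equals u. One patient ranks below another with the same p only when D(1 − u) is smaller. For A this product is 5 × 0.8 = 4. A 14-day patient falls below A once 14(1 − u) < 4, that is, u > 0.714.

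**Does adjustment remove this?** The recorded total is the product of hours in pain and (1 − u). A sedation term added to a linear model does not undo a multiplicative loss, and it does not recover hours that were never rated.

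**Limit of the ratio.** The constant 30% in the last column follows from assuming the same p in rated and unrated hours. If the shares are p_a in assessable hours and p_u in the others, the overall share is (1 − u)p_a + u·p_u. The ratio then differs from it by u(p_a − p_u).

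**The case against.** The strongest reply is that a table cell in a condensed article is being asked to carry operational detail. Who rates the VAS, how often, what score counts as pain and how unrated hours are coded may all stand in a full protocol or analysis plan that is not shown. That is right, and their absence is not the point here. What the article does fix is the metric, a cumulative total, and the instrument, a VAS. That pairing has the weakness shown above unless a further rule is added.

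A second reply is that adjustment is already foreseen. The abstract sends the ICU-stay and ventilation groups to the regression, and in Table 1 those groups contain the Ramsay variable, APACHE II and days on ventilation. This stands and reduces the concern, but it supplies no denominator.

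Third, cumulative exposure is a legitimate construct, and a ratio discards it. This is a fair reason to keep the raw total as a secondary description.

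Fourth, pain is one of seven NSO items, and the Data analysis section does not name it among its example predictors. This limits the reach of the point. That list is open-ended, however, and the abstract places the NSOs as a group in the model.

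**Conclusion.** The point holds as a weakness in how one component of the main exposure is defined. As specified, the variable confounds pain with assessability and days on ventilation, so its association with HRQL may be biased by an amount and in a direction that cannot be known in advance. It should be fixed, but it does not threaten the study as a whole.

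The conclusion rests on two assumptions: that the VAS needs a patient able to indicate a score, and that a material share of ventilated hours is unratable. The article says nothing on who rates the scale. It tracks sedation daily but gives no frequency.

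A reader might infer three stronger things, and the documents support none of them:

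- **Unrated hours are coded as pain-free.** No such rule is stated. Adding nothing to the total is a consequence of using a sum without a denominator.
- **The sickest patients will appear to have the least pain.** Totals also grow with days on ventilation, so the ranking can go either way, as patients C and E show. The simple ordering follows only when days and true pain are held equal, as in A against B.
- **The study would find pain unrelated to HRQL, or protective.** That depends on values of D, p and u, and on model choices, that the article does not give.

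**What to change.** 1. From the charts already reviewed daily, record for each patient the number of hours (or assessments) in which a VAS was obtained.
2. State that hours without a rating are missing, and report assessable hours per patient.
3. Make the analysis variable hours in pain divided by assessable hours, or total hours in pain with assessable hours as a covariate. Enter it together with the Ramsay and days-on-ventilation variables already planned for the model.
4. Keep the raw total as a descriptive or sensitivity variable.
5. Do not use the Glasgow Coma Score to identify unratable hours, since Table 1 schedules it from ICU discharge and not daily. The daily Ramsay item describes sedation but is no hour-by-hour map, so the count in step 1 has to be captured directly.
6. If the chart already holds an observer-rated pain score, abstract it as a separate variable and do not merge it with the VAS.

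The cost is one extra field and a redefined variable, with no change to patient care. Patients who were never assessable have no pain value and need their own category. If they are dropped instead, the analysis selects on sedation. The share also assumes that pain is as frequent in unassessable as in assessable hours, which should be stated as a limitation.
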